### Treatment as usual

All participants will receive treatment as usual which will be the standard care offered to women at this stage of their treatment for cancer. Women will be invited to an in person or remotely delivered end of treatment summary meeting with a breast cancer nurse involving a holistic needs assessment and provision of information relating to local services that can be accessed. Follow-up is patient-initiated, whereby the majority of patients are discharged from hospital follow-up, but are given contact details of a breast cancer nurse that they can speak with if they have any problems or concerns. The breast cancer nurse can make referrals to an oncologist, surgeon or other healthcare professional as needed. The content of treatment as usual received by participants will be collected for all participants in the trial.

### ACTION intervention plus treatment as usual

All participants in this group will receive treatment as usual in addition to the ACTION intervention. The ACTION intervention was co-designed with women affected by breast cancer and healthcare professionals. It is designed to enhance psychological flexibility as a means to improve AET adherence and quality of life, while also being brief, and deliverable without significant changes to NHS services and staffing. The ACTION intervention is comprised of one individual ACT session (1 h) followed by three group sessions (90 min each). Sessions will be delivered by practitioner psychologists remotely using locally approved videoconferencing software and will be digitally recorded, with the agreement of the participant. Within the first session, participants will also be directed to a bespoke ACTION website containing supplementary ACT exercises and additional information regarding HTs and advice on managing treatment side-effects. In addition, a printable participant manual that includes all exercises to be undertaken in the four sessions will be sent to participants.

The ACTION intervention’s format, aims and content are described in Table 2. The initial session is delivered by a practitioner psychologist, and they will be accompanied by a qualified member of staff for the group sessions. Access to home practice exercises will be via the ACTION website and in the participant manual. The manual will be sent to participants after the individual session by the therapists. The group sessions will include between 8 and 10 participants; however they can run with a minimum of three confirmed attendees. A participant will be deemed to have received the intervention if they have attended the individual session and at least one of the three group sessions.

**Table 2 Tab2:** Format, aims and content of the ACTION intervention

Session	Aim	Indicative content
**Individual session** (60 min)	- Assessment of psychological flexibility - Relationship building - Identify some clinically relevant behaviours - Provide a simple formulation	- Explanation of ACT and the ACTION intervention - Conversations exploring a) ongoing treatment and breast cancer experiences and how challenging experiences are managed b) where participants values might lie - Communication of a psychological flexibility formulation - Highlight the ACTION website including ideas for managing side-effects Home practice - ‘Getting to your core values’ exercise - ‘What do you do with difficult feelings?’ exercise
**Group session 1** (90 min)	- Enhance awareness of thoughts, feelings and actions - Introduce a values-based framework for making decisions - Introduce ways to relate to difficult thoughts and feelings	- Education: normalising emotional responses to challenging events - Discussion of ‘What do you do with difficult feelings?’ exercise - Introducing defusion to support living with challenging thoughts: - Experiential defusion practice, e.g. ‘thoughts as hands’ exercise ‘I am having the thought that … ’ exercise Home practice - Defusion diary: noticing what thoughts tend to draw one in and practicing defusing from them
**Group session 2** (90 min)	- Develop deeper awareness of values - Consider hormone therapy decisions while considering values - Introduce willingness skills	- Reflection on the ‘Getting to your core values’ exercise - Values compass - Personal reflection on: ‘what is the smallest possible step you could do to get in touch with your values’ - Reflection on whether treatment adherence or side-effect management is a values-consistent behaviour - ‘Passengers on the bus’ exercise Home practice Smallest possible step exercise Defusion diary
**Group session 3** (90 min)	- Enhance awareness of getting caught up in unhelpful stories - Introduce ideas for stepping back from stories - Reinforce new useful skills	- ‘Notice who is noticing’ exercise - ‘Letting go of unhelpful labels’ exercise - Reflection on what has and has not been useful over the course of the intervention. Reminder of the website including ideas for managing hormone therapy side effects

The intervention was co-designed prior to the COVID-19 pandemic. We subsequently altered the method for delivering the intervention with support from patient representatives from face-to face delivery in a hospital setting to remote delivery using videoconferencing software. Participants are invited to attend from their own homes, while therapists are based at the hospital site or their home, in line with the standard practice for their clinical service.

Participants allocated to the ACTION intervention will be contacted by the psychology team delivering the treatment sessions. They will also be reminded about the ACTION website and encouraged to look at it prior to the session. The first session of the ACTION intervention will take place within 3 months of randomisation. The first group session will take place within six weeks of the first individual session.

#### Participant website

The provision and content of a website was suggested by attendees of the co-design workshop (39), and designed by the research team with support from patient representatives. It contains sections on side-effect management, patient stories (via HealthTalk.org), ACT resources and exercises, and signposting for further information/support. The CTRU will email participants allocated to the ACTION intervention with log in details to the study specific website prior to the first session.

### Therapist training, competency and fidelity assessment

As a novel intervention, we are particularly interested in designing training to enhance competency, and to assess the extent to which therapists deliver ACT with fidelity and deliver all ACTION study procedures.

#### Therapist training

All therapists will receive training in the ACTION intervention, which was designed and will be delivered by CG and JC. They are both registered clinical psychologists with experience in ACT and supporting women with breast cancer, respectively. Training will be delivered remotely over two full days via video conferencing software. The training will outline the psychological challenges of living with breast cancer and HTs, general ACT principles and the practice of ACTION intervention-specific therapy methods. To ensure consistency in intervention delivery, therapists will be given a comprehensive printable training manual and PowerPoint slides to support the group sessions. To assess whether therapists achieve sufficient knowledge of ACT principles, we will assess knowledge of ACT processes after training [43]. They will be offered fortnightly ACT group supervision (60 min) with CG via video conferencing software, and can also access local clinical supervision (JC) as required.

A pool of therapists will be trained at the central delivery site to accommodate attrition. If a therapist is unavailable, efforts will be made to identify a second therapist from the pool of therapists. If no therapist is available from the pool, an additional therapist will be identified from within the clinical service. Prior to delivering an ACTION session, they will be asked to view a recording of the training sessions, and attend a 1–2 h booster session with CG to ensure competency.

#### Competency

To support the establishment of competency CG will analyse the audio recording of the first individual session of all clinicians delivering the intervention, rate their performance against the ACT Fidelity Measure (ACT-FM) [44] and review the therapist checklist. The therapists will receive prompt feedback, and additional training will be offered where appropriate.

#### ACT fidelity

At the end of study, two independent assessors with expertise in ACT-based psychological interventions will listen to ten randomly selected therapy tapes and rate them for ACT fidelity using the ACT-FM. A minimum of one session will be reviewed from each therapist involved.

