## Methods

### Design

This is a multi-site, exploratory, two-arm, individually randomised pilot RCT with a nested qualitative study. Eighty women with early stage breast cancer will be randomised (1:1) to receive treatment as usual or treatment as usual plus the ACTION intervention. The study has been approved by the York and South Yorkshire Health Research Authority Research Ethics Committee (20/YH/0104), and is a registered clinical trial (ISRCTN12027752). The study is presented according to recommendations of the SPIRIT [40] and CONSORT extension for pilot and feasibility trials [41] (Appendix 1). The intervention being evaluated is described using the TIDieR checklist [42] (Appendix 1).

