**THERAPIST**											
ACTKQ	Questionnaire	Therapist		X							
Demographics	CRF	Therapist			X						
ACT-FM	Questionnaire	Independent Expert Reviewer							X		
Procedural Fidelity Checklist	CRF	Therapist				X	X	X	X		
Clinician competency using ACT-FM*	Questionnaire	ACTION Trainer				X					

^*^Reviewing audiotapes from the first individual session of the nominated lead at each site, the reviewer will complete an ACT-FM form

**Table 5 Tab5:** Primary and secondary endpoints recorded within the ACTION trial

Primary endpoints	Secondary endpoints
Number of patients screened for eligibility	Intervention adherence for patients in the intervention arm (number of sessions attended, number of participants in group sessions, whether homework was completed, reasons for non-attendance/non-compliance)
Number and proportion of patients eligible out of those screened and reasons for ineligibility	Website use (tracking data to include number of visits, pages visited, materials downloaded, videos watched, clicked links)
Number and proportion of patients consenting to randomisation out of those eligible and reasons for non-randomisation	Number of patients deemed as having completed the intervention
Number of participants randomised per site per month	Treatment as usual content in both arms from participants (number of sessions attended and content of sessions) and sites (initiatives implemented during the trial)
Questionnaire completion rates at each time-point	Safety (deaths, hospitalisations related to the intervention, RUSAEs)
Number of items of missing data per questionnaire at each time-point	Acceptability of the ACTION intervention to participants (acceptability and B&N questionnaires)
Number and proportion of randomised participants lost-to-follow-up	Number, proportion and timing of therapist withdrawals and reasons for withdrawal
Number, proportion, type and timing of participant withdrawals out of those randomised and reasons for withdrawal	Qualitative study
	Competency and fidelity of the delivery of the ACT intervention by NHS therapists (ACTKQ, ACT-FM, Procedural fidelity checklist)
	“Proof-of-principle” exploration in outcome and process variables
	Estimation of the intracluster correlation coefficient

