**11**	**How well (planned)**	Clinician fidelity to competently deliver the intervention in line with ACT will be assessed by an external rater with a background in ACT. They will complete the ACT-FM checklist while listening to the audio recording of ten sessions. A score of above 28 (out of 72) is considered competent. Additionally, an intervention specific metric of “Procedural Fidelity” is included, which measures other aspects of the intervention that are important for treatment fidelity but are not ACT-specific (e.g. giving worksheets, presenting information etc.). It includes 7 items for session 1 (individual session), 10 items for the first group session, 9 items for the second group session, and 8 items for the third group session. A percentage score is created for each session by dividing the score achieved by the maximum possible score achievable within that session, and multiplying by 100.
**12**	**How well (actual)**	*<To be completed post study>*

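### An unstratified draw of ten tapes under-samples the group sessions for fidelity rating, and the tables disagree with the text on what is rated and by whom

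*Protocol article*

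**What the plan says.** The ACT fidelity section of the protocol article has two independent assessors who, at the end of the study, "will listen to ten randomly selected therapy tapes and rate them for ACT fidelity using the ACT-FM". One condition is added: "A minimum of one session will be reviewed from each therapist involved". Session type is not mentioned.

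Other parts of the article describe the same work differently:

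- Table 4 lists the independent ACT-FM, completed by an "Independent Expert Reviewer", with a single mark in the column for the third group session.
- TIDieR item 11 (Appendix 1) keeps ten sessions but says that fidelity "will be assessed by an external rater with a background in ACT", which is one rater and not two.
- For the separate competency check, the Competency section says that the trainer "will analyse the audio recording of the first individual session of all clinicians delivering the intervention", and TIDieR item 4 agrees. The Table 4 footnote has instead "Reviewing audiotapes from the first individual session of the nominated lead at each site", although the Setting section names a single delivery site.

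**The concern.** Objective iii asks whether NHS therapists can deliver the intervention remotely with fidelity, and the abstract lists competency and fidelity of delivery among the progression criteria. Most of what participants receive is group work, but a random draw from all tapes follows the number of tapes and not the amount of intervention. Each woman generates her own individual tape, whereas one group tape covers eight to ten women.

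No other independent rating fills the gap. The trainer's competency rating uses individual sessions only. The procedural fidelity checklist covers all four sessions, but therapists complete it themselves, and TIDieR item 11 says that it covers aspects that are not specific to ACT. A fidelity result could therefore be reported, and used for progression, with thin evidence on the group component. The conflicting tables add that two readers could carry out the rating differently and both claim to follow the protocol.

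**Working it through.** The article gives no figure for the expected mix of tapes, so there is none to reproduce.

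**Inputs from the article**
- Intervention arm: 80 women randomised 1:1, so 40 (Design).
- Sessions: one individual of 60 minutes and three group sessions of 90 minutes (ACTION intervention plus treatment as usual). Group share of sessions: 3/4. Group share of contact time: 270/330 = 82%.
- Group size: 8–10 planned, minimum three confirmed attendees (same section).
- Tapes rated: 10 (ACT fidelity).

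**Assumptions**
- All 40 women attend, and every session gives one usable tape.
- The draw is a simple random sample without replacement.
- The one-per-therapist rule is not modelled, because the number of therapists is not stated.

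**Formulas.** With G groups, there are 3G group tapes and the pool is T = 40 + 3G.
- Expected group tapes = 10 × 3G/T.
- P(k group tapes) = C(3G, k) × C(40, 10 − k) / C(T, 10).
- P(at least one of the three group sessions unrated) = 3m₁ − 3m₂ + m₃, where mⱼ = C(T − jG, 10) / C(T, 10).

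**Planned group size**
- Groups of 10: G = 4, T = 52, 12 group tapes. Expected 10 × 12/52 = 2.31. P(none) = 5.4%. P(at most one) = 26.1%. P(a group session unrated) = 3(0.4135) − 3(0.1568) + 0.0536 = 82.3%.
- Groups of 8: G = 5, T = 55, 15 group tapes. Expected 10 × 15/55 = 2.73. P(none) = 2.9%. P(at most one) = 16.9%. P(a group session unrated) = 3(0.3512) − 3(0.1091) + 0.0290 = 75.5%.

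**Sensitivity to group size**

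| Group size | Groups | Group tapes / pool | Expected group tapes of 10 | At most one | A group session unrated |
|---|---|---|---|---|---|
| 10 | 4 | 12/52 | 2.3 | 26% | 82% |
| 8 | 5 | 15/55 | 2.7 | 17% | 76% |
| 6 | 7 | 21/61 | 3.4 | 7% | 63% |
| 5 | 8 | 24/64 | 3.8 | 5% | 58% |
| 3 | 13 | 39/79 | 4.9 | 1% | 40% |

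If 30 women attend instead of 40, groups of 8–10 give 2.3–2.9 expected group tapes, so the result depends little on attendance.

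**Table 4 taken literally.** If only third group sessions are rated, no individual session and neither of the first two group sessions enters the sample. That is the opposite mix from the unstratified draw.

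**The case against.** The article does not say that session type is ignored. A random draw can be stratified, and the full protocol or SAP may do so. This stands as a caution: the figures describe the draw as worded, not a known intention. But the article does state the one condition that governs the draw, by therapist, and Table 4 points to a different sample.

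The one-per-therapist rule could also pull in group tapes, because a second staff member joins for group sessions only. If such staff count as therapists, the under-sampling is milder. The article does not say whether they do or how many there are, so the effect cannot be sized.

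The ACT-FM measures how therapists work and not session content, so sampling by therapist does fit objective iii. That is a reason to keep the therapist rule. It does not show that skill in a one-to-one session carries over to leading a remote group.

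Table 4 is a timing table, and its mark at the last session may only mean that rating follows delivery. That is plausible, but the table does not say so.

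A reader might infer that the sample is bound to be mostly individual sessions and that group fidelity will hardly be tested. The documents do not support this. Even at the planned size two or three group tapes are expected and the chance of none is only 3–5%. At the minimum group size the mix is about half and half, and Table 4 read literally implies group tapes only. A reader might also want the first individual sessions, already used for trainer feedback, removed from the pool. The case for that is weak: they are genuine delivered sessions, the end-of-study assessors are different people, and removing sessions held before feedback could inflate measured fidelity.

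**Conclusion.** The group component is under-sampled for the fidelity question. At the planned group size, the draw as worded gives 23–27% group tapes on average, for a component that makes up three-quarters of the sessions. It also leaves a 76–82% chance that one of the three group sessions is never independently rated. With groups as small as three that chance is still 40%. The figures rest on full attendance and recording and on a draw with no therapist constraint.

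The contradictions hold whatever the group size: which sessions the independent raters hear (a random draw against the third group session only), how many raters there are (two against one), and whose first session is rated for competency (all clinicians against a lead at each site, with one delivery site). The competency conflict concerns the trainer's check and does not alter the end-of-study sample. None of this invalidates the trial. It is a cheap improvement to a measure that feeds a progression decision.

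**What to change.** Keep ten tapes and the minimum of one per therapist, but stratify the random draw by session type so that each of the four sessions is rated. One example is four individual tapes and two from each of group sessions 1–3, which gives six group tapes. Leave first individual sessions in the pool.

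The cost is listening time. The example takes 4 × 60 + 6 × 90 = 780 minutes per assessor. The unstratified draw is expected to take 600 + 30 × 2.31 = 669 to 600 + 30 × 2.73 = 682 minutes. The increase is 14–17%, or roughly 100–110 minutes per assessor. Rating takes place at the end of the study, so nothing changes for participants or therapists.

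Reconcile the Competency and ACT fidelity sections, Table 4 with its footnote, and TIDieR items 4 and 11, so that they agree on which sessions are rated, how many assessors there are, and whose first session is rated for competency. State whether supporting staff in the group sessions count as therapists for the one-per-therapist rule.

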#### Procedural fidelity

We will also review therapist self-reports of fidelity to ACTION specific procedures via inspection of the Procedural Fidelity checklist.

### Measures

The measures collected and their timing are illustrated in Tables 3 and 4. Primary and secondary endpoints are described in Table 5.

**Table 3 Tab3:** Summary of assessments and timing

Assessment	Source	Method of completion	Timeline			
			Screening	Baseline	3 months	6 months (for patients recruited at least 3 months prior to the planned end of recruitment)
**PARTICIPANT**						
Screening	Screening CRF	Research nurse/delegate	X			
Contact details	CRF	Research nurse/delegate		X	CTRU to be notified of address changes	
Demographics including comorbidities (Charlson Comorbidity Index)	CRF	Self-completion/research nurse/delegate		X		
Eligibility (including inclusion and exclusion criteria)	CRF	PI/research nurse/pis delegate		X		
Consent	Consent Form	Self-completion/RN/delegate over the telephone		X		
Randomisation	CRF/CTRU Online system	Research nurse/delegate		X		
ASK-12	Questionnaire	Self-completion		X	X	X
McGill Quality of Life-Revised	Questionnaire	Self-completion		X	X	X
Work and Social Adjustment Scale	Questionnaire	Self-completion		X	X	X
HFRDIS	Questionnaire	Self-completion		X	X	X
MAF	Questionnaire	Self-completion		X	X	X
PROMIS Pain Interference	Questionnaire	Self-completion		X	X	X
DIVA (Part C)	Questionnaire	Self-completion		X	X	X
GAD-7	Questionnaire	Self-completion		X	X	X
PHQ-9	Questionnaire	Self-completion		X	X	X
FACT-ES	Questionnaire	Self-completion		X	X	X
Valuing Questionnaire (VQ)	Questionnaire	Self-completion		X	X	X
UK Cancer Costs	Questionnaire	Self-completion		X	X	X
Acceptability	Questionnaire	Self-completion				X
B & N Questionnaire	Questionnaire	Self-completion				X
Safety Reporting	CRF	Research nurse/PI/delegate/self-completion		X		
Usual Care Data	CRF	Researcher/delegate/self-completion		X	X	X

**Table 4 Tab4:** Summary of therapist, fidelity and competency assessments and timing

Assessment	Source	Method of completion	TIMELINE								
			Pre-therapist training	Post-therapist training	Baseline	Individual therapy session	1st group session	2nd group session	3rd group session	3 month follow-up	6 months follow-up
**THERAPIST**											
ACTKQ	Questionnaire	Therapist		X							
Demographics	CRF	Therapist			X						
ACT-FM	Questionnaire	Independent Expert Reviewer							X		
Procedural Fidelity Checklist	CRF	Therapist				X	X	X	X		
Clinician competency using ACT-FM*	Questionnaire	ACTION Trainer				X					

^*^Reviewing audiotapes from the first individual session of the nominated lead at each site, the reviewer will complete an ACT-FM form

**Table 5 Tab5:** Primary and secondary endpoints recorded within the ACTION trial

Primary endpoints	Secondary endpoints
Number of patients screened for eligibility	Intervention adherence for patients in the intervention arm (number of sessions attended, number of participants in group sessions, whether homework was completed, reasons for non-attendance/non-compliance)
Number and proportion of patients eligible out of those screened and reasons for ineligibility	Website use (tracking data to include number of visits, pages visited, materials downloaded, videos watched, clicked links)
Number and proportion of patients consenting to randomisation out of those eligible and reasons for non-randomisation	Number of patients deemed as having completed the intervention
Number of participants randomised per site per month	Treatment as usual content in both arms from participants (number of sessions attended and content of sessions) and sites (initiatives implemented during the trial)
Questionnaire completion rates at each time-point	Safety (deaths, hospitalisations related to the intervention, RUSAEs)
Number of items of missing data per questionnaire at each time-point	Acceptability of the ACTION intervention to participants (acceptability and B&N questionnaires)
Number and proportion of randomised participants lost-to-follow-up	Number, proportion and timing of therapist withdrawals and reasons for withdrawal
Number, proportion, type and timing of participant withdrawals out of those randomised and reasons for withdrawal	Qualitative study
	Competency and fidelity of the delivery of the ACT intervention by NHS therapists (ACTKQ, ACT-FM, Procedural fidelity checklist)
	“Proof-of-principle” exploration in outcome and process variables
	Estimation of the intracluster correlation coefficient

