Following informed consent, confirmation of eligibility and receipt of the baseline questionnaire, participants will be randomised by the research site using the University of Leeds Clinical Trials Research Unit (CTRU) randomisation system. Participants will be randomised on a 1:1 basis to receive either treatment as usual or treatment as usual plus the ACTION intervention and will be allocated a trial number. A computer-generated minimisation programme that incorporates a random element will be used to ensure treatment groups are well-balanced for the following stratification factors: recruiting site, recruitment route (recently completed treatment vs. experiencing medication problems vs. retrospective screening), participant age (≤ 50 years vs. > 50 years and < 70 years vs. ≥ 70 years).

Participants, therapists, research nurses/delegates at site, participant’s GP and staff at the Clinical Trials Research Unit (CTRU) will be not be blinded to the randomised allocation. Following randomisation the research nurse will notify the participant of their allocation, and the therapists will be informed about participants allocated to the intervention arm.

All participants will be requested to complete a follow-up questionnaire at 3 months post-randomisation. Participants recruited at least 3 months prior to the end of the recruitment period will also be invited to complete a questionnaire at 6 months post-randomisation. Participants will have the option to receive questionnaires by post or online. Non-responders will be reminded using postal, telephone, online and text prompts.

A clinician may decide that a participant should be withdrawn from the intervention if there is reason to believe they have become unsuitable for the study. Participants can also withdraw from one or more of the following: intervention, data collected from them via questionnaires or data about them from medical records.

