### Analysis

A detailed statistical analysis plan will be written before any analysis is undertaken. The analysis will focus on descriptive statistics and confidence interval estimation rather than formal hypothesis testing and no formal evaluation of safety or efficacy of the study interventions will be conducted. All analyses will be undertaken on the intention-to-treat population, with all participants included in the analysis according to their randomised allocation, and regardless of non-adherence to the intervention or withdrawal from the study. Final analysis will be conducted once all available outcome data is received.

Descriptive summaries will be presented overall, by arm and by site (where relevant) using appropriate frequencies and summary statistics. Outcome measures will be scored according to relevant scoring manuals. To generate evidence of proof of principle, the mean change from baseline in the three and 6-month ASK-12 scores in both arms will be reported, together with a range of confidence intervals around the main estimate to inform us as to the likelihood of where the ‘true’ estimate may lie. Analysis will adjust for the minimisation factors.

The trial is not powered to provide a precise estimate of the level of clustering relating to therapist effects, but we may be able to investigate this effect. If a sufficient number of therapists are involved in delivering the intervention, we will estimate the intraclass correlation coefficient and produce a range of confidence intervals (e.g. 95%, 67% and 51%) around this to inform the sample size of the definitive trial.

The semi-structured interviews will be analysed using thematic analysis [63].

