### Safety

In this population, we expect episodes of acute illness, infection, new medical problems and deterioration of existing medical problems to occur. These could result in prolonged hospitalisation, hospital re-admission, significant or permanent disability or incapacity, or death. In recognition of this, events fulfilling the definition of a serious adverse event will not be reported in this study unless the event resulted from administration of any research procedure and fulfils definition of a related and unexpected serious adverse event (RUSAE). Deaths will be recorded, but not subjected to expedited reporting. Hospitalisations will be recorded by contacting sites at the end of the study. Pregnancies will also be reported to the CTRU.

All RUSAEs occurring from the date of consent until the end of researcher contact will be reviewed by the Chief Investigator and be subject to expedited reporting to the Sponsor and the main research ethics committee by the CTRU on behalf of the CI within 15 days.

Concerns over patient safety will be monitored by reviewing responses to pre agreed ‘red flags’ assigned to the PHQ-9 questionnaire (if question 9 is answered 1–3 at any time point). If this occurs in the baseline questionnaire, the Chief Investigator (or delegate) will be notified within 2 working days of receipt at the CTRU and will contact the patient to follow up and repeat the screening questionnaire with them to make sure they are (a) not a danger to themselves or others, and (b) still eligible. If this response is given during the follow-up questionnaires the Chief Investigator (or delegate) will be notified within 2 working days of receipt at the CTRU and will report this to the PI at the recruiting site. If the patient is still receiving trial treatment, the psychology team at the central delivery site will be informed and will contact the patient and repeat the screening questionnaire as above.

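### The hospitalisation part of the Table 5 safety endpoint counts only intervention-related admissions, which cannot occur under treatment as usual, although the Safety section sets no such limit on what is recorded

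*Protocol article*

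**What the plan says.** Table 5 of the protocol article gives the safety endpoint, a secondary endpoint, three components: "Safety (deaths, hospitalisations related to the intervention, RUSAEs". Only the middle component carries a relatedness condition in the table.

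The Safety section describes what is collected:
- On deaths: "Deaths will be recorded, but not subjected to expedited reporting".
- On admissions: "Hospitalisations will be recorded by contacting sites at the end of the study". No condition of relatedness or arm is attached.
- Other serious adverse events are not reported "unless the event resulted from administration of any research procedure and fulfils definition of a related and unexpected serious adverse event (RUSAE".
- The reporting window is also stated: "All RUSAEs occurring from the date of consent until the end of researcher contact will be reviewed by the Chief Investigator".

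The same section expects intercurrent illness in this population and says of such events: "These could result in prolonged hospitalisation, hospital re-admission, significant or permanent disability or incapacity, or death".

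The Study processes section says that participants, therapists, site research staff, GPs and trials unit staff "will be not be blinded to the randomised allocation". The Analysis section plans descriptive summaries split by arm, and states that "no formal evaluation of safety or efficacy of the study interventions will be conducted".

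**The concern.** The endpoint is narrower than the data collection that feeds it, and the article gives no reason for filtering admissions but not deaths in the same line. The filter chosen is one that only the intervention arm can pass. A by-arm table of this component would set a judged count against a structural zero. It would say nothing about whether admissions differed between the arms.

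Attribution is also a weak tool here. Where admissions for other causes are expected, deciding whether a particular one was caused by a short psychological programme is difficult. The article does not say who decides for admissions that are not RUSAEs. Counting all admissions by randomised arm avoids the judgement.

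At stake is one descriptive line that the team planning the phase III trial could have had from data the pilot already intends to gather.

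**Working it through.** The documents state no hospitalisation rate and no safety-related precision or power, so there is no figure to reproduce. The check is mainly a comparison of sections, followed by an illustration.

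**1. Can each component occur in each arm?**

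| Component | Restriction stated | Treatment as usual | Intervention |
|---|---|---|---|
| Deaths | None | Possible | Possible |
| Hospitalisations (Table 5) | Related to the intervention | Not possible | Possible, if judged related |
| Hospitalisations (Safety section) | None | Possible | Possible |
| RUSAEs | Resulting from any research procedure | Possible | Possible |

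Control women do not receive the sessions, and website log-ins go only to those allocated to the intervention. Under the Table 5 wording the control count is therefore 0 of 40 whatever happens to those women. RUSAEs differ because their trigger is any research procedure from consent onwards. Control women also consent and complete questionnaires.

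**2. What does the restricted component add?** A serious admission that is related to a research procedure and unexpected is already a RUSAE. As worded, the hospitalisation component mainly adds admissions that are related but expected. A count of all recorded admissions would add information that the other two components do not hold.

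**3. How much would an unrestricted count show?**

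Inputs:
- n = 40 per arm (Sample size section; 80 women randomised 1:1).
- All-cause risk p of at least one admission per woman, the same in both arms: assumed 5%, 10% and 20%. These values are not in the documents.
- Admission data available for all 40 women in each arm (assumed).

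Formulas:
- Expected women admitted per arm = 40p
- Chance of at least one in an arm = 1 − (1 − p)^40
- Approximate 95% half-width for the difference = 1.96 × √(2p(1 − p)/40)

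| p | 40p | Chance of at least one | Half-width |
|---|---|---|---|
| 5% | 2 | 1 − 0.95^40 = 87% | 1.96 × √0.002375 = 0.096 |
| 10% | 4 | 1 − 0.90^40 = 98.5% | 1.96 × √0.0045 = 0.131 |
| 20% | 8 | 1 − 0.80^40 = over 99.9% | 1.96 × √0.008 = 0.175 |

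The half-widths are thus about 10, 13 and 18 percentage points. The normal approximation is rough when only 2 events are expected, but adequate for showing the scale. An unrestricted count would very probably be non-zero in each arm, and it would be far too imprecise to establish or exclude a difference.

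**The case against.** The strongest case on the other side has four parts.

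- **Safety comparison is not an aim of this pilot.** The Analysis section rules out formal evaluation of safety, and none of the four objectives is a safety comparison. This stands, and it limits the importance of the point. It does not remove it, because the change asks for no test, only that a planned descriptive summary be informative.
- **The restriction has a rationale.** The Safety section explains that unrelated serious events are expected and so are not reported, and the Independent monitoring section calls the risk low. That explains limiting serious event reporting. It does not explain narrowing the endpoint for admissions when the same section says that admissions are recorded.
- **Nothing is shown to be lost.** The statistical analysis plan and full protocol are not shown and may tabulate all recorded admissions. That is fair, and it would be wrong to infer that the data are discarded. But the article itself fixes the endpoint wording, so the mismatch between Table 5 and the Safety section is a stated one and not an omission.
- **Unblinded attribution is unavoidable.** Relatedness to a psychotherapy can be judged only by someone who knows it was received, and the article does not say who judges it for ordinary admissions. This stands against any claim that the judgements will be biased. It also favours showing a count that needs no such judgement.

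A reader might go further and infer that the arms cannot be compared on safety at all, or that only deaths are comparable. The documents do not support that: deaths are unrestricted, and RUSAEs are tied to any research procedure, so both can occur in either arm. The fault is confined to the hospitalisation component.

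**Conclusion.** The point holds for one component of one secondary endpoint. As worded in Table 5, hospitalisations are a structural zero under treatment as usual and depend on a relatedness judgement in the intervention arm, while the Safety section records hospitalisations without that limit. Deaths and RUSAEs are unaffected.

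Severity is minor and the change is a free improvement. The gain is a descriptive by-arm summary of perhaps 2 to 8 women per arm at the assumed risks, not a reliable comparison.

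The conclusion rests on two readings: that control women have no access to the intervention, and that the Safety section's unqualified reference to hospitalisations means all of them in both arms. The second is the natural reading, although the section does not use the word all. The size of the gain rests on the assumed admission risks.

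**What to change.** Reword the safety row of Table 5 along these lines: *deaths; all recorded hospitalisations by arm, with those judged related to the intervention shown as a subset; RUSAEs*. State that the summary is descriptive only. In the Safety section, add a phrase confirming that hospitalisations are recorded for both arms regardless of relatedness, so that the two places agree.

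The cost is one line in Table 5, a clarifying phrase in the Safety section and one extra row in the safety table. On the reading above, the data are already due to be collected from sites at study end, so no new data collection, sample size change or analysis method is needed.
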